As a resource considered safe, inexpensive and easy to administer, tDCS could contribute to the rehabilitation of these children, as its neurophysiological effects have been demonstrated to favor the learning of new voluntary motor and postural control strategies. Considering the complexity of brain activity dysfunctions observed in ASD, we need to investigate whether anodal tDCS may (or may not) contribute to motor training results. In addition, it is necessary to understand what are the effects of facilitating cortical excitability of fundamental structures of motor control, such as, for example, the primary motor cortex and the cerebellum. This information may benefit future clinical indications of tDCS for rehabilitation of children with ASD. However, the scientific literature is extremely limited regarding the effects of tDCS on areas of motor control in children with ASD.

The main goal of the present study is to compare the effects of ten 20-min sessions of neurofunctional motor training combined with anodal tDCS over the primary motor cortex, cerebellar region and sham stimulation on motor ability in children with ASD. Specifically, the aim is to determine whether anodal tDCS over these areas of the brain can optimize the effects of gait and postural control training on gross and fine motor skills, mobility, functional balance, motor cortical excitability, cognitive aspects and behavioral aspects in children with ASD. Our central hypothesis is that all individuals will present functional improvements following gait and balance training, but the benefits will be more evident after the administration of active tDCS (primary motor cortex and cerebellar region) compared to the group receiving sham tDCS due to the neurophysiological effects on cortical excitability. Moreover, we believe that the effects of anodal tDCS over the primary motor cortex will be restricted to motor outcomes, whereas the effects of anodal stimulation over the cerebellar region will also be found in outcomes related to cognitive and behavioral aspects.

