
### Statistical analysis

2.5.

The precision of all data will be verified by two researchers and a blinded statistician will conduct all analyses. The Kolmogorov–Smirnov test will be used to determine the distribution of the data regarding adherence to the Gaussian curve. Parametric data will be expressed as mean and standard deviation or 95% confidence interval. Nonparametric data will be expressed as median and interquartile range. Two-way analysis of variance (ANOVA) followed Tukey’s *post hoc* test will be used to assess the effects of tDCS on the outcome variables. For all analyses, the fixed independent variables will be group (active tDCS over the primary motor cortex, active tDCS over the cerebellum and sham tDCS) and assessment time (pre-intervention, post-intervention, follow-up 1 and follow-up 2). The dependent variables will be the outcomes studied. The effect size (Cohen’s d) will be calculated from the difference in the values obtained during the pre-intervention, post-intervention, first follow-up and second follow-up assessments comparing the three groups. Predictive response factors will be identified through logistic regression analysis. Logistic regression models will be performed with the outcomes: type of daily medication, ASD severity, MEP (presence or absence) and pre-intervention MABC-2 result. The level of significance will be set at 5% (*p* < 0.05) and Statistical Package for the Social Sciences (SPSS, version 21.0) will be used for the analyses.

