### Expected results

2.9.

We believe that the three intervention groups will exhibit improvements in motor skills, mobility and functional balance directly related to gait and balance training. However, the effect size is expected to be larger in the experimental groups involving motor training combined with active tDCS (motor cortex and cerebellum) compared to the control group (sham tDCS) with regards to the motor outcomes. We also expect the effects obtained in the experimental groups to be maintained at the follow-up evaluations four and eight weeks after the end of the interventions. Lastly, we expect the motor effects to result in an improvement in the global performance of the children with ASD who participate in the study, including cognitive and behavioral aspects assessed using ADOS and CARS.

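### Section 2.5 gives the tDCS effect to a two-way ANOVA plus Tukey's test without making the group-by-time interaction or any contrast of change against sham the deciding test

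*Protocol article*

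**What the plan says.** Section 2.5 (Statistical analysis) names one procedure for the treatment effect: a two-way ANOVA followed by Tukey's post hoc "test will be used to assess the effects of tDCS on the outcome variables". It then sets the factors: "For all analyses, the fixed independent variables will be group", with the three arms as levels, and "assessment time (pre-intervention, post-intervention, follow-up 1 and follow-up 2". Pre-intervention is therefore an outcome level, not a covariate. The section does not mention the group-by-time interaction, does not say which means Tukey's test covers, and does not say which comparison decides.

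The same section plans Cohen's d, which "will be calculated from the difference in the values obtained during" the four assessments, the last item reading "second follow-up assessments comparing the three groups". This is an effect size, not a test.

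The Introduction states the hypothesis: "all individuals will present functional improvements following gait and balance training, but the benefits will be more evident after the administration of active tDCS", compared with the sham group. Section 2.9 (Expected results) repeats that all three arms should improve, and adds: "We also expect the effects obtained in the experimental groups to be maintained at the follow-up evaluations".

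**The concern.** Every arm receives the same training and every arm is expected to improve. The effect of tDCS is therefore the difference between arms in change from pre-intervention. Tukey's test compares pairs of means, and the result depends on which means it is given.

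- Given the three group means, it compares averages over all four assessments. One of these precedes treatment, where no effect can exist.
- Given the 12 group-by-time means, it compares cells. Some pairs lie within an arm, some between arms at one visit, and some differ in both. No pair is a difference in change.

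If the analyst falls back on the within-arm pairs, the conclusion can become that active stimulation worked because its pre-to-post test was significant and the sham test was not. That is not a comparison of the arms. With about ten children per arm, such a split can arise by chance when all arms improve equally. The expectation that effects are maintained has the same gap: a non-significant week-1-to-week-8 comparison within one arm does not show a maintained advantage over sham.

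**Working it through.** **The plan's own figure.** Section 2.2 gives 24 children (8 per group), raised to 30 for 20% dropout, with an effect size of 1.39 and a balance change of 2.4 (SD 1.70). The usual two-mean formula, two-sided 5% and 80% power, with d = 2.4/1.70 = 1.41, gives 8 per group; 3 × 8 = 24, and 24/0.8 = 30. With d = 1.39 it gives 9 per group, with 79.4% power at 8. The stated size is thus consistent with a single unadjusted comparison of two means, although the article does not name its formula.

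**What Tukey's test compares on 12 cells.**
- All pairs: 12 × 11/2 = 66.
- Within one arm: 3 arms × 6 pairs of times = 18.
- Between arms at the same visit: 4 visits × 3 pairs of arms = 12, of which 9 are post-baseline.
- Different arm and different visit: 66 − 18 − 12 = 36.
- Between-arm differences in change: 0. Such a contrast involves four cells, not two.

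**What it compares on three group means.** If the effect is 1.39 SD at each of the three post-treatment assessments and zero before treatment, the averaged difference is (3/4) × 1.39 = 1.04 SD.

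**Cost of the large family for the useful comparisons.** Take active versus sham at one post-treatment visit, 10 per arm. The critical t is q/√2 and the noncentrality is 1.39 × √(10/2) = 3.11.

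| Family | Error df | Critical t | Power |
|---|---|---|---|
| 3 means at one visit | 27 | 2.48 | 73% |
| 12 cell means | 108 | 3.34 | 41% |

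This treats 1.39 as a difference in units of the SD at one visit. Section 2.2 ties it to a change and its SD, so this use is an assumption.

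**The misleading within-arm pattern.** Simulation with 10 per arm, four assessments, the same improvement in every arm and no tDCS effect. Tukey's test covers the 12 cells. The entry is the share of trials in which at least one active arm is significant from pre-intervention to week 1 and sham is not (within-child correlation 0.5 / 0.7).

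| Improvement in every arm | Within-child (repeated-measures) error | Independent error |
|---|---|---|
| 0.5 SD | 8% / 17% | 0.3% / 0% |
| 0.75 SD | 24% / 36% | 2.8% / 1.0% |
| 1.0 SD | 37% / 22% | 13% / 7% |
| 1.39 SD | 15% / 1% | 34% / 30% |

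The rate peaks where each within-arm test has middling power, and falls when improvement is too small or too large for the arms to split. The article does not give the correlation or the improvement expected in every arm, and does not say which error term will be used.

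**What the interaction does in the same situation.** In a separate simulation with 8 or 10 per arm, the group-by-time interaction with a within-child error term rejects in 4.3% to 5.8% of trials, close to the nominal 5%. With the ordinary two-way error term it rejects in 0% to 0.1%. If the within-arm results are read only after a significant interaction with a within-child error term, the misleading pattern falls to about 1% to 3% for improvements of 0.5 to 1.0 SD. Section 2.5 states no such condition.

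**The case against.** The strongest reply is that a two-way ANOVA on group and time ordinarily includes their interaction, and that the interaction tests exactly whether the arms change differently. This is right, and so a reader should not infer that the plan has no test of differential change. What remains is that section 2.5 does not give the interaction the deciding role. A significant interaction on 6 degrees of freedom also does not say which arm beats sham, or at which visit. The Introduction and Discussion ask about each active arm against sham and about the two sites against each other, and Tukey's step is what the article assigns to that.

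Second, under randomisation a same-visit difference between arms after treatment has the same expectation as the difference in change, so nine of the 66 comparisons do address the tDCS effect. Equal improvement does not trigger them: with independent error, any such active-versus-sham rejection occurred in about 1% of trials, whether or not the arms improved. This stands. These comparisons are usable, but they ignore baseline and may carry the penalty of a 12-mean family.

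Third, nothing in the article says that within-arm tests will decide. The hypothesis is framed against sham, and the Cohen's d sentence compares the three groups. A reader might infer that equal improvement will be reported as a tDCS effect; the article does not say so. The risk is one of interpretation left open.

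Fourth, the full plan may settle the contrasts. Leaving out detail would be no fault in a condensed article. Here, however, the article names the inferential procedure, and the post hoc step it names does not match its hypothesis.

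**Conclusion.** The point holds in a limited form. Section 2.5 sends the tDCS effect to an ANOVA and Tukey's test, with baseline as an outcome level, and makes neither the interaction nor a contrast of change against sham decisive. Tukey's comparisons cannot replace such a contrast. The stronger statement, that the analysis never examines differential change, is not supported, because the ANOVA interaction does so overall.

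On size: the 66, 18, 12 and 36 counts are exact for a 12-cell family. The loss of power from 73% to 41% assumes that family, 10 per arm, and a 1.39 SD difference at one visit. The dilution to 1.04 SD assumes Tukey's test on group means and an equal effect at all three later assessments. The misleading within-arm pattern ranges from about 0% to 37% over correlations of 0.5 to 0.7, improvements of 0.5 to 1.39 SD and two error terms. It can be frequent, but the article does not allow one to say that it will be.

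**What to change.** In section 2.5, replace the post hoc sentence with wording to this effect:

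1. The tDCS effect is judged by three pre-specified between-arm contrasts of change from pre-intervention (or of baseline-adjusted values) at one named primary visit: motor cortex minus sham, cerebellum minus sham, and motor cortex minus cerebellum.
2. The contrasts are taken from the repeated-measures group-by-time model, with a within-child error term and Tukey adjustment over these three only.
3. Within-arm pre-to-post comparisons are descriptive and support no claim about tDCS.
4. Whether effects are maintained is judged from the active-minus-sham contrasts of change at weeks 4 and 8.

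The Cohen's d sentence suggests that the authors already have differences between assessments, compared across arms, in mind, so this fits their intent. The cost is one paragraph of analysis text. No visit, measurement or child is added.

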**Figure 1 fig1:**
[figure not shown]
List of specific time points on this line. Motor training associated with tDCS (active or sham) at a frequency of five sessions per week for two consecutive weeks (total of ten sessions). MABC-2, Movement Assessment Battery for Children-2; PBS, Pediatric Balance Scale. TUG, Timed Up and Go; ADOS, Autism Diagnostic Observation Schedule; CARS, Childhood Autism Rating Scale.

The study will involve the following visits:

Visit 1: Screening of participants according to the eligibility criteria and signing of the statements of consent.Visits 2 and 3: Initial assessment (pre-intervention) one week prior to the onset of the intervention, with the investigation of motor ability, mobility, functional balance, motor cortical excitability, cognitive aspects and behavioral aspects. After the initial assessment, the participants will be randomly allocated to the different intervention groups. These visits will be held on two non-consecutive days and will last a maximum of 1.5 h.Visits 4 to 14: Ten intervention sessions in accordance with the allocation to the different groups. Sessions will be held for two consecutive weeks at a frequency of five sessions per week (Monday to Friday) with a maximum duration of approximately 45 min, 20 min of which will be tDCS combined with motor training.Visits 15 and 16: Post-intervention assessment one week after the end of the intervention with the investigation of motor ability, mobility, functional balance and motor cortical excitability. These visits will be held on two non-consecutive days and will last a maximum of 1.5 h.Visits 17 and 18: First follow-up assessment four weeks after the end of the intervention, with the investigation of motor ability, mobility, functional balance, motor cortical excitability, cognitive aspects and behavioral aspects. These visits will be held on two non-consecutive days and will last a maximum of 1.5 h.Visits 19 and 20: Second follow-up assessment eight weeks after the end of the intervention, with the investigation of motor ability, mobility, functional balance, motor cortical excitability, cognitive aspects and behavioral aspects. These visits will be held on two non-consecutive days and will last a maximum of 1.5 h

Figure 2 displays the flowchart of the study in accordance with the SPIRIT statement (61).

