Withdrawal criteria: Participants who decline to continue in the study, those not present on the days of the experiment and those who miss up to two of the 10 intervention sessions will be removed from the study.

**Randomization procedure:** Randomization will be performed using a program for the generation of random numbers to allocate the participants to one of the following interventions:Experimental group 1 – Motor cortex stimulation: anodal tDCS over the primary motor cortex combined with neurofunctional motor training;Experimental group 2 – Cerebellar stimulation: anodal tDCS over the cerebellar region combined with neurofunctional motor training;Control group – Sham stimulation: sham tDCS combined with neurofunctional motor training.

Randomization will be performed considering stratification based on the severity of ASD according to the Brazilian version of the Childhood Autism Rating Scale (CARS-BR) (63). The randomization sequence will be generated for each category (mild, moderate and severe) with adequately organized distribution in sequentially numbered opaque envelopes.

**Blinding:** After the inclusion of participants based on the eligibility criteria and after the pre-intervention assessment, the allocation of the participants will be informed to the researcher who will carry out the intervention. The researcher in charge of the randomization process will not participate in any other aspect of the study and will not have access to the participants. The researchers involved in the assessment procedures, the participants and their families will not be aware of the allocation of the participants. This information will be provided to the families and participants after the complete conclusion of the procedures of the study. The investigator in charge of the interventions will not be blinded to the allocation of the participants, as it will be necessary to select the active or sham stimulation option of the equipment.

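### The efficacy ANOVA uses the baseline score only as a level of time and omits the CARS-BR stratum used to randomise, which costs some precision but causes no bias

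*Protocol article*

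**What the plan says.** Section 2.5 (Statistical analysis) names the efficacy method, "Two-way analysis of variance (ANOVA) followed Tukey’s" post hoc test, and then its terms: "For all analyses, the fixed independent variables will be group" (three levels) and assessment time (four levels, the first being the pre-intervention visit).

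Section 2.2 (Participants, randomization procedure) says: "Randomization will be performed considering stratification based on the severity of ASD according to the Brazilian version of the Childhood Autism Rating Scale". A separate sequence is prepared for each of three categories: mild, moderate and severe.

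Section 2.1 (General study design) places the "Initial assessment (pre-intervention) one week prior to the onset of the intervention", before allocation, so both variables are known at randomisation. Within section 2.5, severity and the baseline motor score appear only in a separate logistic regression on response factors, whose list reads "type of daily medication, ASD severity, MEP (presence or absence) and pre-intervention MABC-2 result". Neither is a term in the ANOVA that tests the treatment hypothesis.

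**The concern.** Two pieces of pre-randomisation information are left unused in the main comparison.

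- **Baseline score.** Making the pre-intervention visit a level of time means that the group-by-time contrast subtracts the whole baseline value. Subtraction over-corrects whenever the correlation ρ between baseline and later score is below 1. Regression on baseline removes only the predictable part and is more precise.
- **Severity stratum.** Stratified allocation balances severity across arms. If severity is prognostic and the model ignores it, a comparison of scores still counts severity differences as residual noise, so its reported standard error is larger than the true one.

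With 10 children per arm, planned down to eight after dropout, a modest loss of precision is worth avoiding when the data to prevent it are already collected.

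**Working it through.** **The plan's own figure.** Section 2.2 gives a balance-category change of 2.4 with SD 1.70, two-sided α 0.05 and power 0.8 (printed as β). By the normal approximation, n per group = 2(1.960 + 0.842)²/(2.4/1.70)² = 15.70/1.993 = 7.88, so 8 per group and 24 in total. Allowing for 20% dropout, 24/0.8 = 30. The stated 24 and 30 reproduce, and they assume no covariate adjustment.

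**Inputs not in the document.** ρ is assumed from 0.3 to 0.9. The share s of outcome variance explained by the CARS-BR stratum is assumed from 0 to 0.4.

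**Baseline adjustment against change.** With equal variances, in units of the score variance:
- change from baseline: 2(1−ρ)
- baseline-adjusted: 1−ρ²
- ratio: (1−ρ²)/[2(1−ρ)] = (1+ρ)/2

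Estimating one slope with 30 children in three groups multiplies the adjusted variance by about 1 + 1/25 = 1.04.

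| ρ | (1+ρ)/2 | net (×1.04) |
|---|---|---|
| 0.3 | 0.65 | 0.68 |
| 0.5 | 0.75 | 0.78 |
| 0.7 | 0.85 | 0.88 |
| 0.8 | 0.90 | 0.94 |
| 0.9 | 0.95 | 0.99 |

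The net saving in variance therefore runs from about 32% down to about 1%. If the ANOVA is taken literally, with no term for child, the comparator is a plain score comparison. The ratio before covariate cost is then 1−ρ²: 0.75, 0.51 and 0.36 at ρ = 0.5, 0.7 and 0.8.

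**Stratum, unadjusted score comparison.** The standard error is overstated by a factor of about 1/√(1−s): 1.00 at s = 0, 1/√0.8 = 1.118 at s = 0.2, and 1/√0.6 = 1.291 at s = 0.4.

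**Simulation check.** 30 children, three arms, three strata balanced across arms, one pre and one post score, 4,000 runs. Standard error of a group contrast in SD units, at ρ = 0.7 and s = 0.2:

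| Analysis | mean reported SE | actual SD of estimate |
|---|---|---|
| post score | 0.448 | 0.399 |
| post score + stratum | 0.397 | 0.399 |
| change | 0.344 | 0.344 |
| change + stratum | 0.344 | 0.344 |
| baseline-adjusted | 0.322 | 0.318 |
| baseline-adjusted + stratum | 0.316 | 0.319 |

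- Baseline adjustment against change: (0.322/0.344)² = 0.88, which agrees with the net figure above.
- Stratum omitted from a score comparison: 0.448/0.399 = 1.12. At s = 0.4 it is 0.454/0.347 = 1.31.
- Stratum omitted from a change contrast: no cost here. When severity was also made to predict change (0.4 SD of extra change per SD of severity), the reported SE was 0.390 without the stratum and 0.342 with it.
- Stratum added to baseline adjustment at s = 0.2: 0.322 to 0.316 at ρ = 0.7 (about 2%) and 0.391 to 0.374 at ρ = 0.5 (about 4%).

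**The case against.** The strongest reply is that this is a preference about efficiency. Randomisation balances severity in expectation, the group-by-time contrast already subtracts baseline, and covariate lists are often left to an analysis plan that is not shown here. Nor is the sentence in section 2.5 strictly a closed list, since the same section uses severity and baseline MABC-2 in a logistic regression; it can be read as naming the two factors of the ANOVA.

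Part of this stands. The loss is one of precision only, and it may be negligible if ρ is near 0.9. But the article does not leave the efficacy model open. It names the method and its terms, and those terms are the less efficient choice on either reading of the ANOVA.

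A reader might infer that the 12% for the stratum is a loss in the planned repeated-measures contrast, to be added to the loss from not adjusting for baseline. It is not. The 12% belongs to an unadjusted score comparison under one assumed value. Differences in severity that are stable over time cancel from a within-child change.

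A reader might also infer that the results would be biased or the sample size wrong. The documents support neither. Leaving out the stratum makes the test conservative, and the 24 and 30 children follow from the stated inputs without any covariate.

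**Conclusion.** The point holds as a recommended improvement. The direction of the baseline gain is certain in large samples for any ρ below 1. Its size cannot be computed from the article, because ρ is not given: at 30 children the variance falls by about 12% at ρ = 0.7, within a range of about 1% to 32%.

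The stratum is the smaller part. Its omission overstates the standard error of an unadjusted score comparison by 0% to about 30% for 0% to 40% of variance explained. It costs little or nothing in a change contrast unless severity predicts change. At 20% explained, including it is worth about 2% to 4% of the standard error once baseline is in the model. These figures assume equal variances over time and one post-intervention score at a time. The validity of the planned comparison is not in question.

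**What to change.** Model the three post-intervention assessments as the response. Use group, time, group-by-time, the baseline value of that outcome and the CARS-BR stratum as fixed effects, and child as a random effect. Report adjusted between-group differences with 95% confidence intervals at each time.

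Two details need stating in advance:

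- **Sparse strata.** Three strata by three arms gives nine cells, an average of 30/9 = 3.3 children each, or 24/9 = 2.7 at the planned minimum. Give a rule for merging severity categories. It should also settle how the three randomisation categories relate to section 2.3.1, which describes the scale as separating mild-to-moderate from severe autism.
- **CARS as an outcome.** Sections 2.9 and 3 treat CARS as an outcome. For that analysis, use its baseline score and leave out the CARS stratum, which would enter the same measurement twice.

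The cost is small: no new data, some extra analysis work and a few degrees of freedom. At a single time point, the residual degrees of freedom fall from 27 to 24 with baseline and two stratum terms. The return may be negligible if ρ is near 0.9.
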